**Figure 2 F2:**
[figure not shown]
‘Intervention’ refers here to interventions performed by the resuscitation teams thanks to use of the emergency manual. Interventions are graded by external assessors as indicated, neutral or not indicated based on the clinical context. The power curves in the figure plot the power to determine, with p≤0.05, that the proportion of interventions deemed indicated exceeds 10% as a function of the true probability that the intervention is indicated. Assuming that the true proportion of interventions deemed indicated is 21%, 75 interventions are required to meet these requirements. Assuming that half of the patients feature one such intervention and the other half two, then 50 patients can be expected to generate 75 interventions.

### Unperformed interventions recommended by the EM

Fifty additional patients where the EM was not used during the pilot study period, and 50 additional patients that presented during the 6-month period preceding EM implementation, are also identified. These 100 patients are selected based on matching to the 50 patients where the EM was used using age, presenting complaint and relevant comorbidities. The EM is accessed to determine whether additional interventions would have been performed, had the EM been used. All interventions—those actually performed as well as those that might have been performed had the EM been used—are then assessed for degree of indication by three external reviewers as described above. The three specialists are blinded to which interventions were actually performed. Analysing these data may suggest that the EM would have improved management had it been used, with the important caveat that many factors that impact on the suitability of interventions may not be fully conveyed in the patient’s chart.

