### EM: protocol for use

EM use during priority 1 management is strongly advocated but not mandatory. The documenting nurse is assigned the specific task of activating the digital EM. Regarding problem and diagnosis checklists, Do-Confirm is the default mode of EM use—the team first manages priority 1 patients without support from the EM. Once the management plan is finalised (a juncture which may be verbally confirmed with the team leader), the documenting nurse then asks the team: “Which checklist should I display?” When a checklist is displayed, the documenting nurse reads aloud each potential intervention or diagnosis for team consideration. The documenting nurse registers on the digital checklist whether each intervention is

Deemed indicated and has already been carried out.Deemed irrelevant or contraindicated.Deemed indicated and will be carried out thanks to EM use.

The physician responsible for patient management has the mandate to request that the EM not be used, to pause or terminate EM use at any time, and to depart from the recommendations featuring on the checklist. Physicians may also request that the EM be displayed directly and used in Read-Do mode or for retrieval of specific information (Sampling mode). Regarding procedure checklists and fact sheets, the default modes of use are Read-Do and Sampling, respectively. After EM use, teams grade the usefulness of the EM on a 1–6 Likert scale prior to logging out. If the documenting nurse logs in to the EM but the EM is not used, the nurse selects among potential reasons for non-use prior to logging out. Teams can also electronically request contact with the investigators to report specific events related to EM use.

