### Educational campaign

An educational campaign targeting all personnel who work in Lund’s RR precedes the implementation of the EM in clinical practice. Evidence for the potential benefits of an EM—including results from a locally performed crisis checklist study^22^—is presented, as well as the protocol for EM use. Documenting nurses during priority 1 patient management are taught to log in to the EM, display and navigate between checklists, open popover windows, record whether interventions were not indicated, done before or thanks to checklist access, record the team’s opinion of the EM’s value, request contact with the investigators, and log out. Documenting nurses carry out these functions in addition to their usual documentation tasks.

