### Data acquisition

The following data pertaining to each priority 1 patient managed during the 6-month period prior to, and the 6-month pilot study period following implementation of the EM in clinical practice, are extracted from Region Skåne’s clinical databases and the national data registry SVAR (Svenska Akutvårdsregistret):

Patient age and sex, presenting complaint and vital signsPresumptive diagnosis in the RRTime spent in the RR, in the ED, and admitted to the hospitalWhether the patient was admitted to the intensive care unit, and if so duration of admission7-day and 30-day mortality

The following data regarding EM use are recorded on a dedicated computer located within the hospital’s firewall each time the EM is activated during the 6-month pilot study period:

Log-in and log-out timesIdentification number of the nurse who logged in, level of the most senior physician who was physically present at the bedside during patient management, and patient identification number (which is immediately encrypted)Checklists and fact sheets that were displayedWhether interventions were performed before or thanks to checklist access when the EM was used in Do-Confirm mode, or whether the EM was used in Read-Do or Sampling mode insteadThe team’s subjective evaluation of the value of the EM according to a 1–6 Likert scaleReasons for EM non-use despite logging inWhether prompt contact with the research team is requested

The following data are extracted from the medical records of 150 selected cases (see below):

Baseline information regarding the patient’s age, sex, known medical background at the time of presentation and current medicationsClinical information regarding the patient’s presentation to the RR: ambulance report, history that can be obtained in the RR, vital signs, physical findings, ECG, bedside blood test results and point-of-care ultrasound findingsAll interventions (investigations and treatments) performed during the patient’s management in the RRWhether the physician was a specialist or resident, and years of experienceFinal hospital diagnosis pertaining to the presentation in the RR

Figure 1 summarises data acquisition during the study period. The primary investigator alone has access to the encryption key. All investigators have access to the anonymised dataset for analysis purposes.

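### In the 100 comparison cases the chart is the only stated source of care given, so an EM item done but not charted looks like one the EM would have added

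*Protocol article*

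**What the plan says.** Under *EM: protocol for use*, the nurse reads out each item of a displayed checklist in Do-Confirm mode. "The documenting nurse registers on the digital checklist whether each intervention is" in one of three states, the first being "Deemed indicated and has already been carried out". The other two are irrelevant or contraindicated, and to be done because of the EM.

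Under *Data acquisition*, the EM-use data are recorded "each time the EM is activated during the 6-month pilot study period". The same section describes the chart source: "The following data are extracted from the medical records of 150 selected cases", including all investigations and treatments given in the resuscitation room. The separate registry and database extract covers demographics, complaint, vital signs, presumptive diagnosis, times, intensive care and mortality. It does not list interventions.

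Under *Unperformed interventions recommended by the EM*, two matched sets are added. One comes from the pilot itself: "Fifty additional patients where the EM was not used during the pilot study period". The other predates the tool and consists of "50 additional patients that presented during the 6-month period preceding EM implementation". For both sets, "The EM is accessed to determine whether additional interventions would have been performed, had the EM been used". Performed and hypothetical interventions are then graded by three specialists who do not know which were performed. The section says the results may suggest that the EM would have improved management, with a caveat that the chart may not convey everything bearing on suitability.

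**The concern.** To say that the EM would have added an intervention, one must know that it was not given. At the bedside, the already-done option screens out care that the team had delivered. The retrospective exercise has no such screen and relies on the chart. A completed but unrecorded item then enters the pool of interventions that the EM would have added.

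Grading cannot repair this. Performed or unperformed status is settled before the specialists see the item, and they are blinded to it. The stated caveats do not cover it either. The one in this section concerns suitability. Those in the strengths and limitations box, in *Ethical and safety considerations* and in *Strengths, limitations and significance* concern factors behind clinical decisions. None addresses whether the chart records that something was done.

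At stake is the reading of a secondary analysis, namely how much indicated care was missed without the EM.

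**Working it through.** **1. The plan's own figure.** *Sample size calculation* claims at least 80% power with 75 interventions, a null rate of at most 10%, a true rate of 21% and α ≤ 0.05. With an exact one-sided binomial test, the smallest r with P(X ≥ r | 75, 0.10) ≤ 0.05 is r = 13. The attained α is 0.034 and the power P(X ≥ 13 | 75, 0.21) is 0.821. The claim reproduces. It concerns the 50 Do-Confirm cases and does not use the 100 comparison cases. The plan gives no figure for the comparison-case analysis.

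**2. Sources for what was performed.**

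| Group | Bedside item log | Chart extraction |
|---|---|---|
| 50 Do-Confirm EM cases | yes, for displayed checklists | yes |
| 50 pilot cases, EM not used | none | yes |
| 50 pre-implementation cases | none possible | yes |

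**3. Effect of incomplete charting.** Let K be the applicable EM items per case, q the share truly performed and u the share of performed items not charted. The documents give none of these, so all values below are assumptions. Over 100 cases:

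- truly unperformed = 100·K·(1 − q)
- done but not charted = 100·K·q·u
- false share of apparent omissions = q·u / (q·u + 1 − q), in which K cancels.

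Example with K = 5, q = 0.80 and u = 0.10: truly unperformed = 500 × 0.20 = 100; false = 500 × 0.80 × 0.10 = 40; apparent = 140; false share = 40/140 = 29%.

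| Truly performed (q) | u = 5% | u = 10% | u = 20% |
|---|---|---|---|
| 60% | 7% | 13% | 23% |
| 80% | 17% | 29% | 44% |
| 90% | 31% | 47% | 64% |

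The better the actual care, the larger the false share, because fewer true omissions remain to dilute it.

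**4. The correction can be computed.** If C applicable items are charted as performed and D are not documented, the estimated number done but uncharted is C·u/(1 − u). In the example C = 500 × 0.80 × 0.90 = 360 and D = 140. Then 360 × 0.10/0.90 = 40, and 140 − 40 = 100 recovers the true count. The 50 EM cases can supply an estimate of u, since they have both log and chart.

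**The case against.** The best reply is that a condensed article need not give extraction rules, and that nowhere does it say an uncharted item counts as unperformed. That is so. The rule is inferred, because the chart is the only stated source and no other rule is given. But the data source and the intended conclusion are both fixed in the text, and the caveat stops at suitability.

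Several stronger readings are tempting, and the documents do not support them.

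- *The EM and comparison groups are compared on different measurements.* Chart extraction is planned for all 150 cases, with the log as an addition in EM cases. *Data analysis* gives only descriptive proportions and names no between-group test of missed items.
- *The error always favours the EM.* It does so only where the item is graded indicated. Under *Impact of EM use on resuscitation team performance*, neutral items count as no added value and non-indicated ones as detrimental.
- *The size can be anchored on the plan's 75 interventions in 50 patients (1.5 each).* That figure assumes patients who already had at least one EM-prompted intervention. The comparison cases are not selected that way.
- *Charting is known to be poor.* Nothing says so. A designated nurse documents care, and the grading examples (antibiotics, liver function tests, CT) are discrete events.

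These points limit the size and reach of the concern. They do not remove it: with the chart alone, done-but-uncharted and not done remain indistinguishable.

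**Conclusion.** The point holds as a limit on what one secondary, descriptive analysis can show. With respect to charting gaps, the number of comparison-case items that the EM would have added is an upper bound. Where the uncharted items are graded indicated, it overstates the case for the EM. The size is unknown: the 7% to 64% range rests wholly on assumed performance and charting rates and illustrates sensitivity, not an expected value. The conclusion assumes that no source beyond the medical record establishes what was done in the 100 cases, since the article names none. The primary outcome, its sample size and its power are not affected.

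**What to change.** 1. In the 50 EM cases, cross-tabulate the items logged as already done against the chart extraction, made without sight of the log. Report the share charted, overall and by broad intervention type, with confidence intervals that allow for several items per patient.
2. In the 100 comparison cases, call items absent from the chart 'not documented' instead of 'unperformed' and present their count as an upper bound. Add a sensitivity analysis that subtracts C·u/(1 − u), using the uncharted share from step 1, also within items graded indicated.
3. Extend the caveat in *Unperformed interventions recommended by the EM* from suitability to whether the intervention was performed.

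A cut-off that drops intervention types charted less than, say, 95% of the time is not advised. If a type occurs once per case, even 50 of 50 charted gives a one-sided 95% lower bound of 0.05^(1/50) = 94.2%; 59 of 59 would be needed to reach 95%.

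The cost is some wording and one cross-tabulation of data already due to be collected. The missed-intervention figure will become less favourable to the EM. The charting share may also not carry over exactly to non-EM and pre-period cases: the log covers only displayed checklists, and in EM cases "Documenting nurses carry out these functions in addition to their usual documentation tasks". The report should say so.

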### EM: content and format

The EM consists of problem checklists, diagnosis checklists, procedure checklists and fact sheets in digital form. The checklists and fact sheets are accessed through a tablet computer located at each of the three resuscitation sections in the RR and displayed on a large screen visible to all members of the resuscitation team. Problem checklists consist of lists of interventions and diagnoses to consider based on the patient’s presenting symptoms. The popover windows display key clinical features suggestive of specific diagnoses. Diagnosis checklists consist of lists of interventions to consider during the management of a suspected diagnosis. Each intervention is associated with a popover window displaying indications, contraindications or risks associated with the intervention, and details regarding how the intervention is performed, as described in a previous study.^22^ Procedure checklists provide step-by-step guidance for the performance of key procedures as well as pictures. Fact sheets provide information such as medical dosages for sedation and anaesthesia for patients of all ages.

The collection of checklists and fact sheets covers the majority of symptoms, diagnoses and situations that may present in the RR, in accordance with the current European Core Curriculum in Emergency Medicine.^34^ The format and design of each checklist or fact sheet is informed by the literature pertaining to emergency and abnormal checklists in the aviation industry,^35–37^ articles on medical checklists^6 38–40^ and a selection of EMs.^41–44^ The content is customised to local circumstances in Lund’s ED (available medications, medication locations, local routines and phone numbers). EM content and format are further developed through iterative, rapid-cycle simulation-based testing and review by specialists, residents, nurses and nursing assistants who work clinically in Lund’s RR. Internet access to the EM is provided to the ED personnel prior to and during the study to allow for familiarisation and suggestions for improvement. Each checklist and fact sheet is approved by at least one specialist in emergency medicine and one nurse, both of whom work clinically in Lund’s RR.

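### For the 100 comparison cases, nothing keeps hindsight out of the list of interventions the EM would have added

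*Protocol article*

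**What the plan says.** The protocol article, under *Unperformed interventions recommended by the EM*, adds two groups to the 50 reviewed EM cases: 50 pilot-period patients in whom the EM was not used, and 50 from the preceding six months. "These 100 patients are selected based on matching to the 50 patients where the EM was used". For these patients, "The EM is accessed to determine whether additional interventions would have been performed, had the EM been used". The pool sent for grading consists of all interventions, "those actually performed as well as those that might have been performed had the EM been used". The three specialists who grade them do not know which were carried out. The section adds one caveat: the chart may not convey everything that bears on whether an intervention was suitable.

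*Data acquisition* describes the source: "The following data are extracted from the medical records of 150 selected cases". That extract holds the presentation in the RR, every intervention given there, and the final hospital diagnosis. Separately, the presenting complaint and the presumptive RR diagnosis are extracted for every priority 1 patient in both six-month periods.

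Live use is described elsewhere. *EM: content and format* says: "Diagnosis checklists consist of lists of interventions to consider during the management of a suspected diagnosis". Under *EM: protocol for use*, the nurse asks the team "Which checklist should I display", one of the three responses recorded for an item is "Deemed irrelevant or contraindicated", and the physician may "depart from the recommendations featuring on the checklist".

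**The concern.** Two things stand between the EM and an additional intervention at the bedside. The team must open a checklist while the diagnosis is still only suspected, and it must then accept the item. Neither has a stated counterpart when the list is built afterwards for the 100 comparison cases, and the record used contains a diagnosis the RR team did not have.

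A patient whose condition was not recognised in the RR shows the problem. With the final diagnosis in view, the list-builder can open the checklist for that condition and credit the EM with its items, although a team working from its own suspicion might have opened a different one. At stake is the statement that the EM would have improved management in patients treated without it. That statement could rest partly on knowledge that the EM's users would not have had.

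**Working it through.** **1. The plan's own figure.** *Sample size calculation* expects 25 + 2 × 25 = 75 interventions from 50 patients, with a null rate of at most 0.10, a true rate of 0.21, α ≤ 0.05 and power of at least 80%. With an exact one-sided binomial test, the smallest r for which P(X ≥ r | n = 75, p = 0.10) ≤ 0.05 is r = 13. The actual type I error is 0.034, and P(X ≥ 13 | n = 75, p = 0.21) = 0.821. The stated power is reproduced. It concerns the 50 EM-use cases only and takes no input from the comparison cases, so this point does not change it.

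**2. Which cases the extract covers.** 50 + 50 = 100 comparison cases, and 100 + 50 = 150, the number of cases in *Data acquisition*. The extract that includes the final hospital diagnosis therefore covers the comparison cases.

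**3. Live use and retrospective review side by side.**

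| Step | Live Do-Confirm use | The 100 comparison cases |
|---|---|---|
| Diagnostic information | Symptoms and suspected diagnosis | Extract including the final hospital diagnosis |
| Choice of checklist | Team answers the nurse's question at the bedside | No rule stated; person not specified |
| Acceptance of an item | Team may reject it; physician may depart from the checklist | No rule stated |
| Blinding while the list is formed | Not applicable | None stated |
| Blinding while items are graded | To whether an item came before or after EM use | To which items were carried out |

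**4. Does the blinding close the gap?** No. It applies to the graders, after the list exists. The comparison cases are graded in the manner of the main review, where two of the three assessors are also unaware of the EM's content. Neither form of blinding reaches the list-builder, and neither hides the final diagnosis.

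**5. Does the grading close the gap?** Only in part. Items that suit neither the patient nor the situation can be graded neutral or not indicated. An item that is right for the final diagnosis, but comes from a checklist the team would not have opened, is likely to be graded indicated, because the assessors grade on the extracted clinical information and nothing withholds the final diagnosis from them. Nor can grading remove an indicated item that a team would have declined.

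**6. Does the caveat cover it?** No. It concerns information missing from the chart. Hindsight is the reverse: information in the chart that the team lacked.

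**7. Size.** A number would need three inputs: how often the checklist chosen with the final diagnosis differs from the one a team would have opened; the share of unperformed listed items a team would have accepted; and how the surplus items would be graded. The documents give none of these.

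**The case against.** The strongest reply is that this is a journal article, and that who opens the EM, with which papers and by which rule, is detail for the full protocol. That is fair as far as it goes, and the full protocol may hold such a rule. But the article does set out this step, its blinding and its caveat. It places the blinding after the list is made and puts the final diagnosis in the extract. If a rule exists, stating it settles the point.

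Second, every hypothetical item is graded, and *Data analysis* reports proportions, not counts. A longer list padded with poor items would lower the proportion graded indicated. This stands: a long list does not by itself flatter the EM. It does not deal with items that look right only in the light of the final diagnosis.

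Third, problem checklists are keyed to presenting symptoms and list diagnoses to consider, so a missed diagnosis need not mean an unsuitable checklist. This too stands, and it limits how often the bias would arise.

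Fourth, the list-builder must know the care given, since an additional item cannot be identified otherwise. That is correct. Seeing the care given is not a flaw, provided the checklist is chosen first.

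A reader might go further and infer that every item on the opened checklist is counted as one that would have been performed, or that the final diagnosis is used to find the checklist. The text supports neither. It speaks of determining whether interventions would have been performed and of those that might have been, and it gives no acceptance rule. The final diagnosis is in the extract and is not withheld, but nothing says it guides the choice.

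**Conclusion.** The point holds as a gap in how the comparison list is built. The list is formed in retrospect from a record containing the final hospital diagnosis, with no stated limit on checklist choice, no counterpart to the team's rejection of items, and no masking of the list-builder or the graders to that diagnosis. This leaves a hindsight bias in favour of the EM that the stated caveat does not cover.

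Its size cannot be computed from the documents. Any multiple would rest on assumed checklist lengths and acceptance shares, and would describe the length of the list rather than the graded proportions that are reported. The conclusion assumes that no rule in the full protocol, which was not available, already closes the gap.

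The reach is limited. The analysis is secondary and descriptive, and the article says only that it may suggest a benefit. The primary outcome and the sample size are unaffected. A reader might also treat this as the analysis on which wider use of the EM depends. The article does not say so: it makes a possible multicentre study depend on the study results in general.

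**What to change.** Before any list is built, fix a two-step procedure.

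1. Choose the checklist or checklists from the presenting complaint and the presumptive RR diagnosis alone. Both are already extracted for every patient. Withhold the final hospital diagnosis from the list-builder at this step, and from the graders throughout.
2. Only then compare the chosen checklist with the care given and mark the items not performed.

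Report the result as *EM-listed items not performed*, and describe it as an upper bound on what the EM would have added, since a team could have declined any of them.

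Beside it, show the uptake share from the pilot's Do-Confirm log: items taken up thanks to the EM, divided by those items plus the items judged irrelevant or contraindicated. Present this as context, not as a multiplier. Teams that chose to use the EM may differ from those that did not and from those in the earlier period, and an average share cannot say which individual items would have been done.

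The cost is a chart packet released in two steps, one rule in the review instructions, and one proportion from a log already kept. The apparent benefit of the EM in these patients is likely to be smaller.

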### Impact of EM use on resuscitation team performance

The final 50 cases where the EM was used in Do-Confirm mode and interventions were performed thanks to checklist access are identified for external review. The final cases during the 6-month study period are selected to allow personnel the opportunity to integrate the new tool within their clinical practice. The degree to which each intervention is indicated is independently assessed by three specialists in emergency medicine. All three assessors are blinded to whether the intervention was performed before or after EM use. Two assessors are blinded to the content of the EM, while one is involved in the development and use of the EM. Interventions are categorised, based on the available extracted clinical information, as indicated (eg, administering antibiotics to the septic patient), of neutral relevance (eg, measuring liver function tests for the patient with suspected benzodiazepine overdose), or not indicated (ie, overinvestigation or overtreatment, for example, ordering CT to rule out pulmonary embolism for a patient with pulmonary oedema). When the three assessors are not in agreement regarding the degree of indication of the intervention, resolution is reached through discussion, and based on majority opinion if no consensus can be reached. Management is deemed improved when interventions categorised as indicated are carried out thanks to EM use. EM use is deemed to not add value if additional interventions are categorised as of neutral relevance. EM use is deemed detrimental if additional interventions are categorised as not indicated.

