### Data analysis

Descriptive statistics are used to analyse EM use data and determine the following (average over and trends throughout the pilot study period):

Frequency of EM use and mode of use (Do-Confirm, Read-Do or Sampling)Which checklists or fact sheets are most frequently accessedTime between login to and logout from the digital EMSubjective degree of EM value and correlation with specific checklists or fact sheets

Descriptive statistics are also used to determine whether EM use is associated with length of stay in the RR, length of hospital admission and mortality. These analyses are hypothesis-generating and not intended to infer causality. For the 150 patients that are externally reviewed, descriptive statistics are used to report the proportions of interventions deemed indicated, of neutral value or not indicated.

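### In the 100 comparison cases, the stated blinding cannot hold for ECG, bedside blood tests and point-of-care ultrasound if assessors receive the extracted clinical information as listed

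*Protocol article*

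**What the plan says.** The section on unperformed interventions adds 100 cases to the 50 EM cases: 50 from the pilot period in which the EM was not used, and 50 from the six months before implementation. The EM is consulted afterwards to see what it would have added. The items graded are "those actually performed as well as those that might have been performed had the EM been used". They "are then assessed for degree of indication by three external reviewers as described above", and "The three specialists are blinded to which interventions were actually performed".

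The procedure referred to is in the section on the impact of EM use on team performance: "Interventions are categorised, based on the available extracted clinical information".

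The Data acquisition section defines what is extracted: "The following data are extracted from the medical records of 150 selected cases". One item on that list, for clinical information, includes the ECG, bedside blood results and point-of-care ultrasound findings. A separate item covers the interventions performed and makes clear that both investigations and treatments count.

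The Data analysis section treats the reviewed cases descriptively: "descriptive statistics are used to report the proportions of interventions deemed indicated, of neutral value or not indicated".

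**The concern.** The comparison depends on the assessor judging each item on its merits, without knowing whether the team did it or the EM would have proposed it. A test result in the case information gives that away for the test in question.

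There are two consequences. First, the assessor can tell some performed items from hypothetical ones, so any preference for or against the EM, or for actual practice, can enter the grade. One of the three assessors in the referenced procedure helped to develop the EM, and blinding is the stated safeguard against such a preference. Second, performed tests can be graded with knowledge of whether they were abnormal, while hypothetical tests never have a result. Either could shift the proportion of EM-suggested items graded as indicated. That proportion is what would suggest that the EM might have improved management.

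**Working it through.** No arithmetic applies. The article's only power figure concerns the primary outcome in the 50 EM cases and has no bearing on this point. The check sets the statements side by side.

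**Inputs**
1. Cases: 50 EM + 50 EM not used + 50 before implementation = 150. The extraction list covers all 150, so it covers the 100 comparison cases (150 − 50).
2. Items graded in those 100 cases: performed and hypothetical together (section on unperformed interventions).
3. Investigations are interventions (Data acquisition). The grading examples confirm it: "measuring liver function tests for the patient with suspected benzodiazepine overdose" and "ordering CT to rule out pulmonary embolism for a patient with pulmonary oedema" are both graded items.
4. Grading uses the extracted clinical information (section on impact of EM use, carried over by the back-reference).
5. That information includes results for three test types: ECG, bedside blood tests and point-of-care ultrasound (Data acquisition).

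**What a result tells the assessor, if the information is supplied as listed**

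| Graded item in a comparison case | Result in the listed information? | What the assessor learns |
|---|---|---|
| ECG, bedside blood test or ultrasound, performed | Yes, if recorded | The test was done |
| Same three types, hypothetical | Never | Probably not done |
| CT | Not listed, done or not | Nothing by this route |
| Non-bedside laboratory test | Not listed, done or not | Nothing by this route |
| Treatment | No result item | Nothing by this route |

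Only the first two rows conflict with the blinding statement. A present result is conclusive. An absent one is only suggestive, because a test may have been done without its result reaching the record.

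**The same test in the 50 EM cases.** There the blinding concerns whether an item came before or after EM use. Items on both sides were performed, so both can have results, and the presence of a result does not separate them.

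**Could results simply be withheld?** The article does not say so. Withholding them throughout would depart from grading on the extracted clinical information, and treatments would be judged without the ECG, blood and ultrasound findings. With single-stage grading, either the results are shown and blinding fails for the three types, or they are hidden and the other items lose clinical context.

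**The case against.** The strongest objection is that the article never itemises what assessors receive. The extraction list also contains the performed interventions themselves, which cannot be handed over marked as performed if blinding is intended. The list and the assessors' material are therefore not identical, and an article may leave the make-up of that material to the full protocol. This stands in part, and it makes the point conditional. It does not remove it, because clinical information is a separate item on the list and is the stated basis for grading, and the article describes no masking of the results within it.

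A reader might infer that assessors can identify every performed investigation. The documents do not support that. Results are listed for three types only, CT is not among them, and liver function tests would be covered only if done at the bedside, which is not stated.

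A reader might also infer that the primary outcome is compromised. It is not, by this mechanism, because all graded items in the 50 EM cases were performed.

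It is also fair to say that the analysis is secondary and descriptive, that the article claims only that the data may suggest benefit, that no formal contrast of performed with EM-suggested items is described, and that two of the three assessors do not know the EM's content. These facts limit the stakes. They do not restore the blinding, and descriptive proportions built on influenced grades are influenced too. The article's own caveat about charts not conveying every factor is a different issue.

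**Conclusion.** The point holds in a limited and conditional form. If the extracted clinical information reaches assessors as listed, the blinding stated for the 100 comparison cases cannot hold for ECG, bedside blood tests and point-of-care ultrasound. The article claims a property that its own grading procedure, followed as written, does not deliver for these tests.

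The size cannot be stated. The article does not say how many graded items fall in these three types, and the direction of any bias cannot be derived from it. The conclusion rests on two assumptions: that the back-reference carries over the whole grading procedure, and that results are neither masked nor the tests excluded from grading. Neither masking nor exclusion is described.

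**What to change.** For the 100 comparison cases only, choose one of two options and state it before grading starts, because an assessor who has seen the results cannot be re-blinded.

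- **Two-step grading.** Assessors first grade ECG, bedside blood tests and point-of-care ultrasound, performed and EM-suggested alike, without the results of those tests. These grades are locked. The results are then released and the remaining items are graded.
- **Narrower claim.** Keep single-stage grading, report these three test types separately, and limit the blinding statement to the other interventions.

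Two-step grading uses the same assessors and charts. It costs a re-ordering of the case material and slightly longer grading, and it leaves less context for a bedside test that was prompted by an earlier result. The narrower claim costs only wording and a split table, but leaves those grades unblinded. No change to the grading of the 50 EM cases is needed on this ground.
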